## Abstract

**Background:**

Patients with liver cirrhosis have a highly elevated risk of developing bacterial infections that significantly decrease survival rates. One of the most relevant infections is spontaneous bacterial peritonitis (SBP). Recently, *NOD2* germline variants were found to be potential predictors of the development of infectious complications and mortality in patients with cirrhosis. The aim of the I*N*CA (Impact of *NOD2* genotype-guided antibiotic prevention on survival in patients with liver Cirrhosis and Ascites) trial is to investigate whether survival of this genetically defined high-risk group of patients with cirrhosis defined by the presence of *NOD2* variants is improved by primary antibiotic prophylaxis of SBP.

**Methods/Design:**

The I*N*CA trial is a double-blind, placebo-controlled clinical trial with two parallel treatment arms (arm 1: norfloxacin 400 mg once daily; arm 2: placebo once daily; 12-month treatment and observational period). Balanced randomization of 186 eligible patients with stratification for the protein content of the ascites (<15 versus ≥15 g/L) and the study site is planned. In this multicenter national study, patients are recruited in at least 13 centers throughout Germany. The key inclusion criterion is the presence of a *NOD2* risk variant in patients with decompensated liver cirrhosis. The most important exclusion criteria are current SBP or previous history of SBP and any long-term antibiotic prophylaxis. The primary endpoint is overall survival after 12 months of treatment. Secondary objectives are to evaluate whether the frequencies of SBP and other clinically relevant infections necessitating antibiotic treatment, as well as the total duration of unplanned hospitalization due to cirrhosis, differ in both study arms. Recruitment started in February 2014.

**Discussion:**

Preventive strategies are required to avoid life-threatening infections in patients with liver cirrhosis, but unselected use of antibiotics can trigger resistant bacteria and worsen outcome. Thus, individualized approaches that direct intervention only to patients with the highest risk are urgently needed. This trial meets this need by suggesting stratified prevention based on genetic risk assessment. To our knowledge, the I*N*CA trial is first in the field of hepatology aimed at rapidly transferring and validating information on individual genetic risk into clinical decision algorithms.

**Trial registrations:**

German Clinical Trials Register DRKS00005616. Registered 22 January 2014.

EU Clinical Trials Register EudraCT 2013-001626-26. Registered 26 January 2015.

## Background

Cirrhosis is the final common pathway of chronic liver diseases [1]. The alcoholic and non-alcoholic fatty liver diseases, as well as chronic viral hepatitis, are the most important causes of cirrhosis. The increasing liver disease rates, with more than 800,000 annual deaths worldwide due to complications of cirrhosis [2], demonstrate the high socioeconomic impact of liver diseases and the need for improved patient care and disease management.

Patients with cirrhosis are approximately ten times more likely to develop bacterial infections than healthy persons [3]. Spontaneous bacterial peritonitis (SBP) and urinary tract infections are observed most frequently [4]. The occurrence of bacterial infections is also highly relevant for the patients’ prognosis, with the overall median mortality of infected patients with cirrhosis quadrupling to more than 60% at 12 months [3]. The prevalence of SBP is 10% in hospitalized patients and 1.5% to 3.5% in outpatients with cirrhosis [5,6]. Although antibiotic therapy reduces the acute mortality of hospital inpatients with SBP, there is a very high probability of recurrence and death (up to 70%) within 1 year after an episode of SBP [7-9].

Long-term antibiotic prophylaxis has been shown in randomized controlled trials to significantly reduce the risk of SBP recurrence [7], and it is thus advised for all patients who have survived an index SBP [10]. The best data exist for fluoroquinolones, especially for norfloxacin [7,11]. Primary prevention of SBP with antibiotics to avoid a first episode is currently not uniformly recommended for patients with ascites, because the existing data are conflicting and the intervention might promote the development of multidrug-resistant bacteria [12-16]. Thus, long-term antibiotic prophylaxis should be administered only to subgroups with the highest risk [10]. In one randomized controlled trial, Fernández and co-workers showed that primary prophylaxis with norfloxacin in a clinically defined high-risk population (protein level of the ascites below 15 g/L and advanced liver failure or impaired renal function) significantly reduced the risk for a first episode of SBP and short-time survival [17].

Recently, the *NOD2* (nucleotide-binding oligomerization domain containing 2; HGVS name: NC_000016.10) germline variants p.R702W, p.G908R and c.3020insC were found to be predictors of the development of infectious complications and mortality in patients with cirrhosis when carriers of the variants died significantly earlier and significantly more often experienced SBP [18]. Bruns *et al*. [19] validated the association between *NOD2* variants and culture-positive SBP. Their study indicated that patients carrying *NOD2* variants presented more frequently with variceal bleeding and hepatocellular carcinoma. Thus, it is the aim of the I*N*CA (Impact of *NOD2* genotype-guided antibiotic prevention on survival in patients with liver Cirrhosis and Ascites) trial to investigate whether survival of a genetically defined high-risk group of cirrhotic patients characterized by the presence of *NOD2* genetic variation is improved by primary antibiotic prophylaxis of SBP.

## Methods/Design

### Trial design and ethical considerations

The trial has been designed to assess the effect of antibiotic primary prophylaxis on survival in carriers of *NOD2* risk variants without SBP. Figure 1 summarizes the design of the study. The I*N*CA trial is a double-blind, placebo-controlled clinical trial with two parallel treatment arms. It is planned to randomly allocate 186 eligible patients to one of these arms (1:1 ratio). Balanced randomization, stratified for the protein content of the ascites (<15 g/L or ≥15 g/L, given that a low protein content is an established risk factor for SBP) and the study center, will be performed as centralized, computer-based block randomization using separate randomization lists for each stratum. Only the central and independent pharmacy (Heidelberg University Hospital) performing the randomization procedure, and neither the investigators nor the patients, will be aware of the allocation sequence or the block size used. Blinding of participants and study personnel responsible for treatment and outcome assessment is ensured by identical encapsulation of placebo and active substance that makes both indistinguishable, as well as by the use of identical blisters and folding boxes. The unique patient randomization number labeled on the boxes makes the medication patient-specific. The confidential block size ensures randomization concealment after emergency un-blinding because of safety reasons or after unblinding due to SBP. Access to emergency envelopes is regulated at all sites.

**Figure 1 Fig1:**
[figure not shown]
**Study flowchart.** Overall, 186 patients meeting the inclusion criteria and no exclusion criteria are randomly assigned to two treatment arms. Especially, present SBP has to be ruled out, and patients have to be verified to carry at least one of the three common *NOD2* variants. It is expected that about 1,400 patients need to be evaluated to finally randomize the calculated 186 patients. SBP, Spontaneous bacterial peritonitis.

The patients allocated to arm 1 receive 400-mg norfloxacin capsules (Norfloxacina ABC; ABC International Pharma, Ivrea, Italy) once daily. In arm 2, the patients receive an identically looking capsule containing no active ingredient (placebo) once daily. The treatment and observational periods are 12 months for both groups. Treatment will not differ between arms.

The study is approved by the leading ethics committee (Ethikkommission der Ärztekammer des Saarlandes; reference number 71/13) and the German Federal Institute for Drugs and Medical Devices (Bundesinstitut für Arzneimittel und Medizinprodukte, BfArM; reference number 4039362). The participating centers’ eligibilities were evaluated by the responsible local ethics committees (University Hospital Bonn: Ethikkommission an der Medizinischen Fakultät der Rheinischen Friedrich-Wilhelms-Universität Bonn; University Hospital Essen: Ethik-Kommission der Medizinischen Fakultät der Universität Duisburg-Essen; University Hospital Frankfurt: Ethik-Kommission des Fachbereichs Medizin der Johann Wolfgang Goethe-Universität Frankfurt; University Hospital Halle: Ethik-Kommission der Medizinischen Fakultät der Martin-Luther-Universität Halle-Wittenberg; University Hospital Hamburg-Eppendorf: Ethik-Kommission der Ärztekammer Hamburg; University Hospital Heidelberg: Ethikkommission der Medizinischen Fakultät Heidelberg; University Hospital Jena: Ethik-Kommission der Medizinischen Fakultät der Friedrich-Schiller-Universität Jena; Westpfalz-Hospital Kaiserslautern and University Hospital Mainz: Ethik-Kommission der Landesärztekammer Rheinland-Pfalz; University Hospital Leipzig: Ethik-Kommission an der Medizinischen Fakultät der Universität Leipzig; University Hospital Mannheim: Medizinische Ethikkommission II der Medizinischen Fakultät; University Hospital Ulm: Ethik-Kommission der Universität Ulm). The I*N*CA trial is registered in the EU Clinical Trials Register (EudraCT 2013-001626-26) and will be conducted in accordance with the Declaration of Helsinki in its latest version, the guidelines of the International Conference on Harmonization of Good Clinical Practice and the applicable German law. In order to ensure patient safety, an external data and safety monitoring board (DSMB) consisting of at least three independent members with a high level of expertise in the conduct of clinical trials, as well as in the fields of hepatology, pharmacology and statistics, will receive unblinded safety and outcome data at defined time points (after inclusion of 10, 60 and 100 patients).

### Participants

In general, all patients with liver cirrhosis and ascites should be screened for the I*N*CA trial. Importantly, only patients verified to carry at least one of the three common *NOD2* risk variants (p.R702W, p.G908R or c3020insC) can ultimately participate in the trial. The most important exclusion criteria are a present SBP or a previous history of such, as well as long-term antibiotic treatment, irrespective of the indication. Table 1 provides a list of the inclusion and exclusion criteria. In this multicenter national study, patients will be recruited at a minimum of 13 participating referral centers. These centers have specific clinical expertise in treating patients with advanced liver diseases, and ten of them are centers for liver transplantation. These centers were also selected because of their experience in conducting randomized, controlled trials, their specialized outpatient structure and their collaboration with local primary and secondary care hospitals. The estimated recruitment period is 24 months, and recruitment started in February 2014.

**Table 1 Tab1:** **Inclusion and exclusion criteria**
^**a**^

**Inclusion criteria**	**Exclusion criteria**
Age ≥18 years.	Age <18 years.
Written informed consent to participate in the clinical trial and written informed consent for genetic testing.	Absent written informed consent to participate in the clinical trial or for genetic testing.
Patients have to be able to understand and follow instructions and to be willing to attend all study visits (compliance).	Patients unable to understand the meaning of the clinical trial and the consequences of study participation.
Presence or history of ascites in case of advanced liver disease compatible with cirrhosis (liver biopsy not required).	Patients unable to understand or follow instructions or not willing to attend all study visits.
Diagnostic paracentesis to exclude SBP within 10 days before the baseline visit. Patients who cannot undergo paracentesis because of small amounts of ascites can only be included in the trial if SBP is unlikely, taking into account clinical and blood test indicators.	Simultaneous participation in another clinical trial (study medication has to be stopped for almost 30 days before the baseline visit).
Positive genotyping result for at least one of the *NOD2* risk variants p.R702W, p.G908R or c.3020insC.	Persistent drug abuse (alcohol abuse may be tolerated in the setting of adequate compliance).
Pregnancy is to be excluded by a pregnancy test (beta-hCG blood test or urine test) in women with childbearing potential who have not undergone surgical contraceptive methods or hysterectomy. These patients have to use effective contraceptive methods.	Pregnancy, planned pregnancy or breastfeeding patients.
	Patients without a history of ascites.
	SBP diagnosed by the index paracentesis within 10 days before baseline.
	Previous history of SBP. (When this is uncertain, absence of a secondary antibiotic prophylaxis may be used as an alternative criterion to exclude SBP.)
	Long-term antibiotic prophylaxis, irrespective of the indication. Long-term treatment is to be completed at least 28 days before randomization.
	Contraindications against norfloxacin or placebo such as the following:
	• Intolerance to norfloxacin, to substances with related chemical structure or to other components of norfloxacin or placebo.
	• Patients with acquired long QT syndrome or other nonmodifiable risk factors causing a persisting corrected QT prolongation (corrected according to Bazett’s formula: >470 ms for men and >480 ms for women).
	• Patients with galactose intolerance, lactamase deficiency or glucose and/or galactose malabsorption.
	• Patients with myasthenia gravis.
	• Patients with tendinitis or tendon rupture linked to fluoroquinolone intake.
	Patients with a life expectancy of less than 12 months due to hepatocellular cancer, other malignant diseases or another severe comorbidity.
	Patients with HIV infection with a CDC classification clinical stage C or laboratory stage 3.

^a^CDC, Centers for Disease Control and Prevention; hGC, Human chorionic gonadotropin; *NOD2*, nucleotide-binding oligomerization domain containing 2; SBP, Spontaneous bacterial peritonitis.

### Objectives and endpoints

The I*N*CA trial design has been chosen to determine whether primary antibiotic prophylaxis with norfloxacin improves overall survival in a high-risk population of patients with liver cirrhosis and ascites defined by the *NOD2* genotype. The secondary aims are to evaluate if the frequencies of SBP and other clinically relevant infections necessitating antibiotic treatment (for example, urinary tract infection, pneumonia, sepsis, bacteremia), as well as the total duration of unplanned hospitalization due to cirrhosis, differ between study arms. Table 2 summarizes the study endpoints. In addition, safety aspects, including the impact of norfloxacin on the intestinal microbiome, will be addressed.

**Table 2 Tab2:** **Study endpoints**

**Primary endpoint**	**Secondary endpoints**
Overall survival after 12 months	Spontaneous bacterial peritonitis within 12 months
	Other clinically significant infections (for example, urinary tract infections, pneumonia, sepsis, bacteremia) requiring antimicrobial treatment within 12 months
	Duration of unscheduled cirrhosis-associated hospitalization within 12 months

### Frequency and scope of study visits and interventions

All patients who have already developed ascites should be screened for trial participation. Particularly, SBP has to be excluded, and ascitic protein content has to be determined by a clinically indicated index paracentesis (maximally 10 days prior to baseline visit). Patients who cannot undergo paracentesis because of small amounts of ascites can be included in the trial only if SBP is unlikely, taking into account clinical and blood test indicators. Hereafter potentially eligible patients must be informed about the study and genetic testing by an investigator with the use of a specific information sheet. Informed consent to study participation and genetic testing is mandatory for a further evaluation of patients, and especially *NOD2* genetic testing, using patients’ blood specimens. At the baseline visit (within 28 days before randomization) and during treatment within the trial, only noninvasive or minimally invasive interventions are scheduled (Table 3). Patients who fulfill all inclusion criteria but no exclusion criteria proceed to randomization. Treatment with the study medication must be initiated within 7 days after randomization. Adverse reactions to the study medication are more likely to occur early after treatment initiation, so that closely scheduled visits are implemented for the first 4 weeks. Thereafter, and for the remainder of the trial, the study visits are less frequent (Table 4) and, at predefined time points only, telephone interviews are scheduled to record any (serious) adverse event (AE) as well as primary and secondary endpoint information. Patients are regularly treated within the trial for 12 months. Patients who must definitely stop the study medication for any reason (for example, SBP,prolongation of QTc above 500ms [QTc; QT interval corrected for heart frequency using Bazett’s formula]) will complete the trial without taking the trial medication and attend the regular visits. Patients with SBP during the trial will be unblinded. Patients who undergo liver transplantation or who revoke their consent to participate are censored for the analysis with the date of withdrawal.

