**Table 4 Tab4:** **Visits and time points**

**Baseline period**	**Within 28 days before randomization**
Visit 1	Day 0 (up to 7 days after randomization)
Visit 2	Day 7 (±2 days)
Telephone visits 1 to 9	Weeks 4, 8, 16, 20, 28, 32, 40, 44 and 48 (±7 days)
Visits 3 to 5	Weeks 12, 24 and 36 (±7 days)
Visit 6	Week 52 (±7 days) or shortly after close-out

Patients are allowed any additional, necessary treatment, which is at the discretion of the physician in charge. However, to avoid treatment bias, any long-term treatment with antibiotics is prohibited, whereas temporary antibiotics for treatment of acute infections are permitted. Study medication can be paused for a maximum of 7 days.

In case of AEs, the investigators at each trial center judge the severity and causality of the AE and decide on an individual basis to continue, pause or terminate the study drug. The compliance of study participants is determined by the ratio of pills actually taken (pills delivered minus pills returned) and pills expected to be taken.

Because treatment with fluoroquinolones rarely causes QT interval prolongation, electrocardiography (ECG) with determination of the QTc is mandatory for safety reasons at baseline, to visit 1 before first intake of study medication as well as to study visits 2 through 6 during trial participation. The actions to be taken in case of marked prolongation of the QTc (ECG controls, modification of concomitant medication, pausing or termination of the study drug) are in line with published guidelines and recommendations [20,21].

At the baseline visit, an ascites sample derived from the index paracentesis is collected and stored. In case of recurrent ascites and suspicion of SBP, a diagnostic paracentesis must be performed (according to standard of care) to diagnose or exclude SBP. In this case, ascites samples are collected. Moreover, stool samples are collected regularly throughout the study (visits 1 through 6) for additional analyses to evaluate the effects of long-term treatment with antibiotics on intestinal microbiome composition (sequence-based analyses investigating absolute and relative abundance as well as diversity of microorganisms; sequence- and culture-based resistance analyses).

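### Routine unblinding at SBP, with follow-up continuing, leaves part of the 12 months potentially open for two secondary endpoints, and more of it on placebo if norfloxacin reduces SBP

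*Protocol article*

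**What the plan says.** Under the trial design heading, the protocol article states: "Blinding of participants and study personnel responsible for treatment and outcome assessment is ensured by identical encapsulation of placebo and active substance". The same paragraph acknowledges that codes will be broken for SBP as well as in emergencies: "The confidential block size ensures randomization concealment after emergency un-blinding because of safety reasons or after unblinding due to SBP".

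The section on visits and interventions sets the rule: "Patients with SBP during the trial will be unblinded". It attaches no condition and does not say who learns the allocation. SBP is also its first example of a reason to stop study medication for good, and such patients "will complete the trial without taking the trial medication and attend the regular visits".

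Table 2 lists three secondary endpoints, each over 12 months. Besides SBP they are:
- for hospital stays, "Duration of unscheduled cirrhosis-associated hospitalization within 12 months"
- for infections apart from SBP, "Other clinically significant infections (for example, urinary tract infections, pneumonia, sepsis, bacteremia) requiring antimicrobial treatment within 12 months"

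Between site visits, "telephone interviews are scheduled to record any (serious) adverse event (AE) as well as primary and secondary endpoint information". The text after Table 4 adds: "Patients are allowed any additional, necessary treatment, which is at the discretion of the physician in charge".

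**The concern.** Identical capsules protect the blind only until the code is broken. From SBP onward, the patient and the site staff may know the allocation while endpoint data are still being collected. Someone has to decide whether an infection is clinically significant and needs treatment, whether to admit, and whether an admission is due to cirrhosis. Each of these decisions could be influenced by knowing the allocation.

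The trigger is also the event that the drug is meant to prevent. If norfloxacin works, more placebo patients are unblinded, and earlier. The two arms would then be compared on endpoints observed partly blind and partly open, in different proportions. A post-SBP difference in infections or hospital days would be harder to attribute to treatment alone.

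**Working it through.** **Which endpoints are exposed**

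| Endpoint | Accrues after SBP? | Depends on decisions open to influence? |
|---|---|---|
| Overall survival (primary) | Yes | No, death is objective |
| First SBP | No, diagnosed before unblinding | Not in this way |
| Other infections needing antimicrobials | Yes | Yes: significance, treatment |
| Unscheduled cirrhosis-related hospital days | Yes | Yes: admission, attribution |

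The exploratory Cox model uses infections requiring antibiotics as a time-dependent variable, so it takes in the same post-SBP data.

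**How much patient time is open**

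The article gives no figure on this point, so there is none to reproduce.

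Inputs from the article: 12-month survival S of 40% on placebo and 60% on norfloxacin, from the sample size section, and 12 months of follow-up.

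Assumed, because the article gives no SBP incidence in *NOD2* carriers: the 12-month SBP risk p in the absence of death, and independent exponential times to SBP and death. Other censoring is ignored.

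With time in years:
- death hazard d = −ln S: 0.916 on placebo, 0.511 on norfloxacin
- SBP hazard a = −ln(1 − p)
- mean total time T = (1 − e^(−d))/d: 0.6/0.916 = 0.655 on placebo, 0.4/0.511 = 0.783 on norfloxacin
- mean blinded time B = (1 − e^(−(a+d)))/(a + d)
- open share = 1 − B/T
- proportion unblinded = [a/(a + d)] × (1 − e^(−(a+d)))

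Worked case, 30% vs 10%:
- Placebo: a = 0.357, a + d = 1.273, e^(−1.273) = 0.7 × 0.4 = 0.28, B = 0.72/1.273 = 0.566. Open share = 1 − 0.566/0.655 = 13.6%.
- Norfloxacin: a = 0.105, a + d = 0.616, e^(−0.616) = 0.9 × 0.6 = 0.54, B = 0.46/0.616 = 0.747. Open share = 1 − 0.747/0.783 = 4.7%.

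| Assumed SBP risk, placebo vs norfloxacin | Open share of patient time | Patients unblinded |
|---|---|---|
| 15% vs 5% | 6.6% vs 2.3% | 9.9% vs 3.9% |
| 30% vs 10% | 13.6% vs 4.7% | 20.2% vs 7.9% |
| 50% vs 15% | 24.1% vs 7.1% | 34.5% vs 11.8% |
| 20% vs 20% | 8.9% vs 9.5% | 13.3% vs 15.8% |

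The roughly threefold ratio in the first three rows comes from the assumed risk ratio. In the last row SBP risks are equal, and the small remaining difference comes only from the better survival assumed on norfloxacin.

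Independence of SBP and death is a simplification. The background section links infection to much higher mortality, and shorter survival after SBP would tend to lower the open shares.

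**The case against.** The strongest reply is that nothing here is hidden and no bias is shown. The trial design section itself names unblinding due to SBP, so a reader who infers that the plan overlooked or concealed the step goes too far. What stands is narrower: the protection described there is of the randomisation sequence for other patients. It does not restore the blinding of the patient whose code was broken.

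Other points stand in full:
- **Who classifies.** The article does not say who classifies the two endpoints. A reader might call them investigator-judged, but that is an inference from their wording and from the discretion given to the treating physician. The full protocol may name a blinded assessor. Even so, the decisions to treat and admit, and what an unblinded patient reports by telephone, could remain open.
- **Reason for unblinding.** The article gives no reason, but that does not show there is none. The discussion notes that quinolone-resistant SBP may carry a specific risk for patients on norfloxacin. Clinical need is not for this review to decide.
- **Imbalance.** A reader might take more open time on placebo as built into the design. It follows only if norfloxacin lowers SBP risk.
- **Bias.** Open time is exposure to possible bias, not bias. Study drug has stopped in both arms by then, and the documents support neither a direction nor a size.
- **Reporting.** Nothing in the article shows that these endpoints will be reported as fully double-blind.

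**Conclusion.** The point holds in limited form. The article states a rule of unblinding at SBP with continued follow-up, and that rule cannot be squared with an unqualified statement that participants and outcome assessment stay blinded. The potentially open part is the post-SBP period, for two of the three secondary endpoints.

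Across the assumed SBP risks of 15% vs 5% to 50% vs 15%, with independent exponential times and the article's survival assumptions, the open part is about 7% to 24% of patient time on placebo and 2% to 7% on norfloxacin. These are illustrations, since none of the SBP risks comes from the article.

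A reader might infer that the confirmatory result is compromised. The documents do not support that: the confirmatory test concerns survival alone, and neither death nor the first SBP is exposed in this way. This is a cheap improvement to the secondary analyses, not a flaw in the main comparison.

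**What to change.** Reconcile the blinding statement in the trial design section with the unblinding rule in the visits section:

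1. Limit disclosure at SBP to those who need the allocation for the patient's care, leaving that need to the investigators. Otherwise, and with existing staff where possible, keep those who conduct the telephone interviews and record these two endpoints unaware of it.
2. Record the date of unblinding.
3. Keep the full 12-month analysis as the main one. Add a supportive analysis of other infections and hospital days up to SBP, related to time at risk, with SBP and death as competing events.
4. In the report, describe post-SBP data on these two endpoints as not fully blinded.

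The cost is a clarified protocol sentence, one date field and one supportive analysis. Where the same physician treats and records, separation may not be possible; the unblinding date then at least shows which data are affected. The supportive analysis has fewer events, and its follow-up ends at a post-randomisation event that treatment may affect, so it should be read only beside the full analysis. No second assessor is required.
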